### Statistical analysis

The original data will be uniformly stored in the paper version of the case report form, and the electronic data will be single-path input and checked by two researchers. The database will be input to Excel software and will be statistically analysed with SPSS 25.0 software. The measurement data of normal distribution will be expressed as X ± S, and the measurement data of skewness distribution will be expressed as M (P25, P75). The Mann-whitney U test will be used for comparison. Enumeration data will be expressed as cases and percentages, and chi-square tests will be used for comparison.

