## Methods

### Study objects

According to the literatures, the estimated sensitivity rates of TBCB and TBLB methods were 80% and 60%, respectively. The estimated prevalence rate of the target subjects is 50%. Using McNemar test with PASS software to calculate the sample size, when the value of ɑ was 0.05, the sample size was 122 cases. And totally 146 hospitalized patients with diffuse lung disease were intended to be enrolled in the study with the amplification of 1.2 times. The specific criteria are as follows:Inclusion criteria

(a) ILD patients with unknown reasons (more than 18 years old), have the necessity to undergo TBCB for the diagnosis; (b) Hospitalized patients need to complete arterial blood gas analysis, blood routine, blood coagulation routine, liver and kidney function, electrocardiogram, immunology examination, chest HRCT, and other examinations; (c) Good compliance and can be coordinated with this study; (d) After being fully informed of the purpose and method of the study, the patients are willing to participate in the study and sign the informed consent.

(2)Exclusion criteria

(a) Do not agree to participate in the study; (b) Have participated in other studies that could affect the observation of this study; (c) Patients who fail to complete the examination required for admission before TBCB or TBLB; (d) Chest HRCT showed non-interstitial lung disease; (e) Any conditions deemed unsuitable for inclusion by the investigators;

(3) Elimination criteria

(a) Patients who do not meet the inclusion criteria or who meet the exclusion criteria after enrollment; (b) After enrollment, patients have poor compliance and could not cooperate with the observers;

(4)Withdrawal criteria

Patients who meet the inclusion criteria and fail to complete the study for some reasons, including patients who voluntarily withdraw and are determined to withdraw by the researchers.

(5)Study end pointsa. Primary end point: The differences in diagnostic efficiency and incidence of operation-related complications between TBCB and TBLB.b. Secondary end point: Analyze the relationship between the time of biopsy and the incidence of complications; the relationship between freezing time, size of specimen and complications; The histopathological results will be handled in a multidisciplinary meeting, to analyze the consistency of pathological, clinical, and radiology.

The research process is shown in Fig. 1.

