### Process of TBCB/TBLB

The patients enrolled will undergo both TBLB and TBCB procedures.

Tracheal intubation, mechanical ventilation, and vital signs monitoring

Sedation and analgesia. Place the bite and No. 8 tracheal catheter under the guidance of a soft bronchoscope. When the distal end of the catheter is located in the middle and lower part of the trachea, the catheter will be fixed. A monitor will monitor the vital signs.

(2)Placement of guide wire

Insert the soft bronchoscope via the nose, enter the trachea through the glottis from the trachea catheter, empty the capsule, and then enter the bronchus. Place the guide wire into the bronchus of the intended biopsy segment through the bronchoscope working passage, and exit the bronchoscope after the catheter is in its place. Fill the capsule and fix the guide wire, and then the guide wire will be strengthened by the respiratory therapist who is responsible for mechanical ventilation so that it will not displace.

(3)Placement and testing balloon

When the soft bronchoscope enters the airway through the tee and tracheal catheter, the assistant will send the balloon via the guide wire into the bronchial opening of the proposed biopsy segment or lobe. The balloon will be filled with air under direct vision and adjusted to completely close the bronchial opening of the proposed biopsy segment or lobe, and it is appropriate to remember the amount of air injected.

(4)TBCB/TBLB

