When the endotracheal intubation is connected to the ventilator or high-frequency ventilation, bronchoscopy will be performed. First, conventional TBLB will be performed with biopsy forceps under the guidance of X-ray, and biopsies will be performed through different segmental bronchi 2 or 3 times in general. The biopsy specimens will be checked by pathologists and performed ROSE on site to guarantee the quality to continue the biopsy. After the biopsy, X-ray fluoroscopy will be performed to check whether there is pneumothorax, and the size of biopsy specimens, bleeding, pneumothorax and operation duration will be recorded. Then, TBCB will be performed at the same site. Freezing probes will be sent to the biopsy site through a bronchoscope work channel with positioning. The bronchoscope and cryogenic probe will be pulled out after refrigeration at a distance of 1 ~ 2 cm away from the pleura for 3 ~ 4 s. Take the biopsy specimen off after thawing. The bronchoscope will reenter into the bronchial to check for bleeding. Biopsy is usually done 2 ~ 3 times. Figure 2 shows the lung tissue obtained by TBCB. Biopsy specimens will be checked by pathologists and will be performed ROSE on site to guarantee the quality for further biopsy. After the biopsy, X-ray fluoroscopy will be performed to check for pneumothorax, and size of the biopsy specimen, bleeding, pneumothorax condition and operation duration will be recorded. In both operations, the next biopsy will be performed in the absence of significant bleeding and pneumothorax. To do another site of biopsy, insert a guide wire into the balloon again, and guide the balloon into the new segment by clamping the guide wire with biopsy forceps, and repeat the preceding process. After the biopsy, mechanical ventilation and tracheal intubation will be removed when the patient regains consciousness, and the patient will be sent back to the ward for monitoring and observation for 4–6 h.

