About the safety of TBCB, it was reported that there were no significant differences in the incidence of pneumothorax, bleeding, and bleeding severity compared with conventional TBLB [20, 21]. Yarmus et al. [22] reported for the first time that TBCB was used to evaluate 11 patients after lung transplantation under a soft microscope and achieved satisfactory results without serious complications. The CHILL study [23] reported that TBCB was associated with mild bleeding (grade 1 bleeding that requiring suction to clear) in 56.2% of patients, but only 16 cases were included in the study. These studies indicated that TBCB had good safety and efficacy in ILD, but they were all retrospective studies with small samples, and prospective studies with large samples are urgently needed in clinical practice to evaluate the diagnostic value of TBCB in ILD.

ROSE is a rapid cytological interpretation technique which accompanies sampling in real time during diagnostic interventional operations. In the sampling of the target sites, under the premise of almost no loss of tissue specimen, part of the sample is printed on the slides to make a cytological substrate, quickly stained and immediately interpreted with a special microscope integrated with clinical information. As a cell carrier, ROSE has the following functions: evaluation quality of the samples, guidance intervention means of operation in real time, forming the preliminary diagnosis or narrowing the scope of differential diagnosis, optimization the processing scheme of the target specimen, analyzing and predicting the outcomes of the disease combined with all clinical and cytological information [24]. However, ROSE has not been applied in ILD at present.

It is a prospective and self-controlled study to evaluate the diagnostic value of TBCB/TBLB combined with ROSE technology in a large sample size of ILD patients. In addition, it is the first time that ROSE technique was used in the diagnosis of ILD. The results of this study will clarify the value of TBCB in the diagnosis of ILD and confirm its safety and effectiveness, which is expected to improve the efficiency of diagnosis and improve the prognosis of ILD patients.

Abbreviations: TBLB, transbronchial lung biopsy; TBCB, transbronchial lung cryobiopsy; ROSE, rapid on-site evaluation.

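### Every patient has both biopsies and the trial is sized with McNemar, but the analysis section names Mann-Whitney U and unspecified chi-square tests and no paired method

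*Protocol article*

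**What the plan says.** The design is within-patient. Under Process of TBCB/TBLB the article states "The patients enrolled will undergo both TBLB and TBCB procedures". Forceps biopsy comes first, and after it: "Then, TBCB will be performed at the same site". The Discussion labels the study accordingly: "It is a prospective and self-controlled study".

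The primary end point (Study objects) is "The differences in diagnostic efficiency and incidence of operation-related complications between TBCB and TBLB". The sample size paragraph in the same section assumes sensitivities of 80% and 60%, a prevalence of 50% and alpha 0.05, and arrives at 122: "Using McNemar test with PASS software to calculate the sample size". This is raised by a factor of 1.2 to 146.

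The Statistical analysis section names two tests. For measurement data: "The Mann-whitney U test will be used for comparison". For categorical data: "Enumeration data will be expressed as cases and percentages, and chi-square tests will be used for comparison". It does not mention McNemar, Wilcoxon signed-rank, a paired t-test or pairing, and it does not assign either test to a particular end point.

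**The concern.** The TBCB and TBLB results come from the same patients, so the two sets of results are likely to be correlated. A Mann-Whitney U test or an ordinary chi-square test treats them as coming from two separate groups and uses a variance without the covariance term. The analysis section then describes a two-group comparison, although the design and the sample size are paired.

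Both parts of the primary end point are affected. For diagnostic efficiency the risk is a needless loss of power. For complications the loss matters differently: the study aims to confirm safety, and a non-significant difference from an underpowered test could be read as equal safety.

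**Working it through.** **1. The sections side by side.** Each patient has both procedures, at the same site; the primary end point is a difference between procedures; the sizing test is paired. The analysis section names one test that is for independent samples (Mann-Whitney U) and one that is unspecified (chi-square). Specimen size and operation duration are recorded after each procedure, so they too give paired values.

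**2. The figure of 122.** The McNemar formula is n = [z(1−α/2)·√pd + z(power)·√(pd − d²)]² / d², where pd is the proportion of discordant pairs and d = 0.80 − 0.60 = 0.20. The article does not give power, sidedness or pd. Assuming a two-sided test, 80% power and pd = 0.32:

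n = (1.960·√0.32 + 0.842·√0.28)² / 0.04 = 60.4, rounded up to 61. Dividing by the prevalence, 61 / 0.5 = 122.

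With the same alpha and power, the total is 74 at pd = 0.20 (the minimum), 168 at pd = 0.44 (independence) and 232 at pd = 0.60 (the maximum). So 122 is attainable with a paired test but is not fixed by the stated inputs. The inflation is consistent: 122 × 1.2 = 146.4. An unpaired two-proportion calculation with the same alpha and power needs 82 target-condition results per method instead of 61.

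**3. Standard error of the difference, 61 patients, pd = 0.32 (correlation 0.31).**
- Paired: √[(0.32 − 0.04)/61] = 0.068, a 95% half-width of 13.3 points.
- Unpaired: √[(0.16 + 0.24)/61] = 0.081, a 95% half-width of 15.9 points.

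**4. Power at 80% versus 60%** (simulated multinomial data, 400,000 replicates, two-sided 5%; the discordance values are assumptions).

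| Patients | Discordance | Correlation | McNemar | Exact McNemar | Chi-square |
|---|---|---|---|---|---|
| 61 | 0.20 | 0.61 | 99.9% | 99.0% | 77.4% |
| 61 | 0.32 | 0.31 | 84% | 77% | 72% |
| 61 | 0.36 | 0.20 | 78% | 70% | 70% |
| 61 | 0.44 | 0 | 69% | 59% | 68% |
| 122 | 0.32 | 0.31 | 98.6% | 97.9% | 96.5% |

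**5. Type I error of the ordinary chi-square, 61 patients, both rates 70% (assumed).** It is 0.5% at discordance 0.20 and 2.5% at 0.32. With the correlation held at 0.31 instead, it is 1.9%. At zero correlation it is 5.0%, and at a correlation of −0.15 it is 6.8%.

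**6. Complications.** The article gives no rates. Assuming 12% with TBCB, 5% with TBLB, 3% with both, and 122 pairs, power is 67% with McNemar, 58% with exact McNemar and 51% with chi-square.

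**7. Mann-Whitney U on paired normal data, 122 pairs** (4,000 replicates). Type I error is 0.9% at correlation 0.5, 2.3% at 0.3, 5.2% at 0 and 6.7% at −0.2. Wilcoxon signed-rank stays between 4.5% and 5.4%.

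**8. One illustrative table of 61 patients** (33 positive on both, 16 on TBCB only, 4 on TBLB only, 8 on neither). McNemar: (16 − 4)²/20 = 7.20, p = 0.007. Unpaired chi-square on 49/61 versus 37/61: 5.67, p = 0.017.

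**The case against.** McNemar's statistic is itself referred to a chi-square distribution, and the article writes of chi-square tests in the plural without naming Pearson's. Since the sample size paragraph names McNemar, the authors may simply have used the term loosely in a condensed article, and a fuller plan may name the paired tests. For the binary end points the contradiction is therefore an inference from the wording. This part stands, and the text needs to be made specific. It does not rescue Mann-Whitney U, which is an independent-samples test on any reading, although it bears on specimen size and operation time and not on the proportions in the primary end point.

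The section also does not tie tests to end points. Chi-square and Mann-Whitney U suit secondary questions that compare different patients, such as freezing time by complication status. That stands too, but no other test is offered for comparing TBCB with TBLB.

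The size of the loss is also open to challenge. The larger gaps use the uncorrected McNemar test. The exact version narrows the gap to about 5 points at discordance 0.32, removes it at 0.36, and is the less powerful choice at independence. The 61-patient basis assumes that the test is confined to target-condition cases; if diagnostic efficiency is analysed in all 122, little is lost. These limits are accepted.

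**Conclusion.** The point holds: the design and sample size are paired, and the tests named for comparison are not stated to be. Under the expected positive correlation, the unpaired tests err on the conservative side and cost power. On the 61-patient basis the loss against uncorrected McNemar is about 12 points at discordance 0.32, with a range from none at 0.44 to over 20 points at 0.20. It is about 2 points with all 122 patients at discordance 0.32. For complications it is about 16 points (about 7 against the exact test) on the assumed rates. Discordance, the 61-patient basis and the complication rates are assumptions; only 80%, 60%, 50%, alpha 0.05 and 122 come from the article.

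Three stronger readings are not supported:
- A reader might infer that all p-values and intervals would be wrong, or that false positives are inflated. No confidence intervals are planned, the means with SD and medians with quartiles are descriptive and unaffected by pairing, and inflation would need negative correlation.
- A reader might infer that a planned power is missed. The article states no power.
- A reader might infer that 122 is wrong. It can be reproduced under plausible inputs.

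**What to change.** In the Statistical analysis section, assign tests to comparisons:
- **TBCB versus TBLB, diagnostic efficiency and complications:** McNemar's test (exact when discordant pairs are few), with the paired risk difference, its 95% CI and the 2×2 concordance table.
- **TBCB versus TBLB, specimen size and operation time:** Wilcoxon signed-rank or paired t-test on per-patient values.
- **Comparisons between different patients**, such as specimen size or freezing time by complication status: chi-square and Mann-Whitney U, as now.

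It would help to state the power, sidedness and discordant proportion behind 122 at the same time.

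The core change is about two sentences. It needs no extra patients or data, the paired tests are standard procedures, and the article reports only one patient enrolled, so the change can be made before any results are known.

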***Collection of clinical data***

Collect relevant information about the operation, including anesthesia method, anesthesia complications, time of TBCB, time of TBLB, freezing time, and operation time;Specimens’ information, including the number and size of specimens, ROSE results, and pathological results;Complications caused by the operation, including bleeding, pneumothorax, infection, and acute exacerbations caused by the operation, as well as the delayed complications mentioned above during the 3 days of follow-up after the operation.Collecting adverse events in the study:

iii.a. Adverse event (AE): Any adverse medical event that occurs during the observation period of a patient during the study, which does not necessarily imply a causal relationship with the procedure.iv.b. Serious adverse event (SAE): An adverse event meeting one or more of the following criteria is considered as SAE, such as death; life threat; persistent or severe disability or permanent loss of function; hospitalization or prolonged stay due to AE; leading to congenital malformation.v.c. Severity classification of adverse events: mild——uninduced or only causing mild discomfort, not affecting daily life and not requiring clinical management; moderate——active narration, affecting daily life, but tolerating, requiring clinical general management; severe——having objective manifestation that cannot be tolerated, surely affecting daily life, needing rest in bed and active clinical treatment.vi.d. Relationship between adverse events and operation: it can be divided into five levels: ① definitely relevant, ② probably relevant, ③ possibly relevant, ④ probably irrelevant, and ⑤ definitely irrelevant. ①, ②, ③ are considered as operation-related adverse events.

(5) Severity of bleeding

Grade 0: no bleeding; Level 1: bleeding that can be stopped by negative pressure suction without other hemostatic measures; Level 2: bleeding that requires local injection of frozen saline, epinephrine, or balloon closure; Level 3: severe bleeding that beyond endoscopic control, resulting in hemodynamic and respiratory instability, requiring vascular intervention or surgical hemostasis, or requiring admission to intensive care unit (ICU).

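### Neither test named in the analysis section is both paired and ordered, so neither suits a within-patient comparison of the 0-3 bleeding grade

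*Protocol article*

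**What the plan says.** All references are to the protocol article.

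- **Design** (Process of TBCB/TBLB): "The patients enrolled will undergo both TBLB and TBCB procedures". TBLB comes first: "the size of biopsy specimens, bleeding, pneumothorax and operation duration will be recorded. Then, TBCB will be performed at the same site". After TBCB the same items are taken again: "size of the biopsy specimen, bleeding, pneumothorax condition and operation duration will be recorded".
- **Scale** (Collection of clinical data, Severity of bleeding): four ordered levels, beginning "Grade 0: no bleeding; Level 1: bleeding that can be stopped by negative pressure suction without other hemostatic measures" and rising to Level 3, bleeding that endoscopy cannot control.
- **Tests** (Statistical analysis): after the sentence on measurement data, "The Mann-whitney U test will be used for comparison". For counts, "Enumeration data will be expressed as cases and percentages, and chi-square tests will be used for comparison". Neither is said to be paired, and no rule is given for ordered categories.
- **Endpoint** (Study end points): the primary endpoint covers diagnostic efficiency and the incidence of operation-related complications. Bleeding severity is not named as an endpoint.
- **Sample size** (Study objects): 122, enlarged to 146, calculated with the McNemar test, which is paired. No distribution of bleeding grades and no power for bleeding is given.

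**The concern.** The bleeding grade has two features that a test should use. It is ordered, and the two grades being compared come from the same patient. Chi-square on the 2x4 table of counts uses neither. It spreads the evidence over 3 degrees of freedom and gives the same result however the grades are permuted. Mann-Whitney U uses the order but assumes independent groups.

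When a patient's two grades are positively correlated, both tests overstate the variance of the difference and reject too rarely. The risk is therefore a missed worsening, not a false alarm. That matters in a trial that aims to confirm safety. The Discussion already cites earlier reports of "no significant differences in the incidence of pneumothorax, bleeding, and bleeding severity compared with conventional TBLB", and a test short of power makes another non-significant result easier to obtain.

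**Working it through.** **Plan's own figure.** None exists for bleeding grade. The 122 is a sample size for sensitivity; 122 x 1.2 = 146.4, which gives the stated 146. I use 122 as the number of complete pairs.

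**Assumptions (not in the protocol).** Each patient's two grades come from a bivariate normal variable cut at the grade shares, with correlation 0 to 0.6. Two patterns of general worsening for grades 0/1/2/3:

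- Pattern A: TBLB 50/40/9/1%, TBCB 40/40/17/3%
- Pattern B: TBLB 42/48/9/1%, TBCB 30/50/17/3%

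**Tests, two-sided 5%.**

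- Chi-square, unpaired and unordered: sum of (O - E)^2/E over the 2x4 table, 3 df.
- Stuart-Maxwell, paired and unordered: d'V^-1 d, where d holds the differences between the two sets of grade totals and V is built from the discordant cells only, 3 df.
- Marginal homogeneity score test, paired and ordered: Z = sum(D)/sqrt(sum(D^2)), where D is TBCB grade minus TBLB grade. Wilcoxon signed-rank gives nearly the same power.

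**Power at correlation 0.3, 122 pairs.**

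| Test | Pattern A | Pattern B |
|---|---|---|
| Chi-square | 47% | 58% |
| Paired, unordered | 58% | 69% |
| Paired, ordered | 74% | 85% |

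**Splitting the loss.** Pairing gives 58 - 47 = 11 and 69 - 58 = 11 points. Order gives 74 - 58 = 16 and 85 - 69 = 16 points. Over correlations 0 to 0.6, order alone is worth about 8-17 points in these patterns. The share due to pairing is near zero at correlation 0 and grows with the correlation.

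**A second set of assumptions.** TBLB 45/40/13/2% with a proportional-odds shift of 2 for TBCB, 122 pairs:

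| Test | Correlation 0 | 0.3 | 0.6 |
|---|---|---|---|
| Chi-square | 66% | 68% | 69% |
| Mann-Whitney U | 82% | 87% | 90% |
| Stuart-Maxwell | 65% | 80% | 93% |
| Wilcoxon signed-rank | 79% | 90% | 98% |

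Here order, with both tests paired, is worth 4-14 points. Mann-Whitney U is close to signed-rank at low correlation and falls behind as the correlation rises.

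**Type I error.** With identical grade shares, chi-square rejects about 3% at correlation 0.3 and 1.4% at 0.6. Mann-Whitney U falls to 0.7% at 0.6. The paired ordered tests stay near 5%.

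**Where the ordered test does worse.** Suppose TBCB only moves patients from Level 1 to Levels 2-3 and Grade 0 is unchanged: 40/50/9/1% against 40/36/21/3%. The ordered paired tests then have about 36-64% power and the unordered tests about 75-88%, over correlations 0 to 0.6. McNemar on Level 2 or higher (large-sample version) has about 90% at correlation 0.3 and 95% at 0.6.

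**The case against.** **The protocol does not assign chi-square to the bleeding grade.** This is correct. A reader might infer the assignment because a grade is naturally shown as cases and percentages, but the text never classes it. The point therefore rests on both named tests: neither is paired, and the design is.

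**The endpoint is incidence, and order plays no part in a yes/no outcome.** This stands, and it limits the weight of the point. It would be wrong to present severity as part of the named primary endpoint. Pairing still matters for incidence.

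**The choice of test can be left to a fuller plan.** In general, yes. Here the article does name its tests, and the ones it names do not fit a scale that it defines itself.

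**The loss is smaller than it looks.** A reader might conclude that chi-square has about half the power. It does not: 47/74 = 64% and 58/85 = 68%, so it keeps about two thirds, and part of the shortfall is pairing.

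**The change is not free of drawbacks.** This stands too: for the Level 1 to Levels 2-3 pattern, which is a plausible harm, the ordered test is the weaker one. Both proposed tests also count a step from 0 to 1 the same as a step from 2 to 3, although Level 3 is far graver.

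**Not every patient will have both grades.** The procedure section lets the next biopsy proceed only without significant bleeding or pneumothorax, so a TBCB grade may be missing after a bad TBLB grade. The figures above assume complete pairs.

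Nor do the documents show that the null results in the cited studies came from unordered tests.

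**Conclusion.** The point holds as a modest improvement to a safety comparison. If bleeding grade is compared between methods, either named test ignores the pairing, and chi-square also ignores the order. Under a general worsening, 122 complete pairs and correlation 0.3, moving from chi-square to a paired ordered test raises power from about 47-58% to 74-85%, of which about 16 points come from order and 11 from pairing.

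These sizes depend on grade shares and correlations that the protocol does not give. They shrink under other uniform shifts and reverse when only Levels 1 to 3 are affected. The type I error result depends less on the assumed effect: with positive within-patient correlation, the unpaired tests reject well below 5%.

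A paired test also cannot separate the method from its position, since TBLB always comes first at the same site.

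**What to change.** In Statistical analysis:

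1. State that bleeding grade is compared within patient with one pre-named paired ordered test, either the marginal homogeneity score test or Wilcoxon signed-rank.
2. Report the 4x4 table of TBLB grade by TBCB grade, with the proportions of patients worse and better on TBCB and their 95% confidence intervals.
3. Compare the yes/no incidence of any bleeding, and of Level 2 or higher, with McNemar. This matches the test used for the sample size and covers the pattern where the ordered test is weak.
4. Count and report patients with no TBCB grade, by their TBLB grade and the reason.
5. Keep ordinary chi-square for unordered categories in independent groups.

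The cost is a few sentences. The tests are available in the named software, no new data are needed, and the Trial status section reports only one patient enrolled. The one statistical cost is the lower power of the ordered test under the Level 1 to Levels 2-3 pattern, which items 2 and 3 are there to help reveal.
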